## Abstract

**Background:**

With aging of the population, the search for alternative models of care adapted to older people with dependency is necessary. In this setting, foster families (1-3 older people per family) could be an alternative to nursing homes, residential care facilities, or community- and home-based care.

**Objective:**

The KArukera Study of Ageing in Foster Families is a prospective cohort study designed to investigate the care pathways of older people with dependency in foster care over a year. The 1-year hospitalization rate (main objective), cost of hospitalization, incidence of mortality, prevalence of geriatric syndromes, and quality of life of residents will be assessed. Quality of life and burnout of their respective foster caregivers will also be studied.

**Methods:**

This study cohort will include 250 older people living in foster families in Guadeloupe (French West Indies), as well as their respective foster caregivers. Both older people and caregivers will be interviewed concurrently on site at three time points: (1) at baseline, (2) at 6 months, and (3) at 12 months. For older people, we will collect anthropometric measures, cognitive impairment, depressive and anxiety symptoms, functional abilities, physical frailty, information on general health status, quality of life, and care pathways (hospitalization, mortality, and medical and paramedical consultations). We will also assess the quality of life and burnout symptoms of family caregivers at each follow-up. A phone update of vital status (alive or death) and care pathways of residents will be carried out at 3 and 9 months after the baseline examination.

**Results:**

Recruitment opened in September 2020 and ended in May 2021, with 109 older people recruited and 56 respective foster caregivers. The 1-year follow-up was ended in June 2022. Data analyses are ongoing and the first results are expected to be published in May 2023.

**Conclusions:**

Foster families are a potentially innovative way to accommodate dependent older people. This study could help define the clinical profile of older people adapted to foster families in the transition from frailty to dependency. The effectiveness of foster families, in terms of hospitalizations and mortality, will be compared with other models of care, particularly nursing homes. In this setting, a twin study carried out in nursing homes in Guadeloupe with similar aims and outcomes will be conducted. Beyond mortality and morbidity, the numerous outcomes will allow us to assess the evolution of geriatric syndromes over time.

**Trial Registration:**

ClinicalTrials.gov NCT04545775; https://clinicaltrials.gov/ct2/show/NCT04545775

**International Registered Report Identifier (IRRID):**

DERR1-10.2196/40604

## Introduction

The Caribbean region is a heterogeneous canvas of autonomous states and dependent territories of sovereign states. In this area, the French West Indies constitute a specific cultural topic. A total of 90% of its population is of African descent. Although the official language is French, the medical and cultural realities are quite different from mainland France. There is little epidemiological data on this population, despite strong specificities, in terms of prevalence of specific diseases (hypertension, diabetes, etc), specific genetic risk factors, and socioeconomic characteristics or access to health care [1].

On January 1, 2016, there were officially 394,110 inhabitants in Guadeloupe, a number that has been decreasing by 0.5% every year since 2011 [2]. This decrease is the result of both a slowdown in demographic growth and a constant negative net migration rate, due to high unemployment rates and lack of economic prospects. As a result, by 2030, people older than 65 could represent 28% of the population [2] and the number of dependent older people should double. This older population will have age-related medical problems, especially chronic (hypertension, diabetes, and cancer) or neuropsychiatric pathologies. An increase in dependency and its associated consequences, such as an increase in hospitalizations and nursing home admissions, is to be expected. Early detection is lacking, and general practitioners cannot compensate for the shortage of medical specialists. In the current context, the economic, medical, social, and human stakes are considerable and finding the appropriate care option for older people with dependency has become a critical issue.

Despite strong family support, living at home is sometimes difficult or impossible for seniors and their caregivers [3] (heavy dependency, exhaustion of caregivers, regular decompensation of chronic pathologies, etc). Moreover, social isolation, social vulnerability, and loneliness among older people living at home [4,5] increase the risk of adverse health events, notably mortality [6]. The most developed and successful model for dependent persons in high- and middle-income countries is the nursing homes. However, the transition from one’s home to a nursing home usually disrupts residents’ social life and lifestyle, and institutionalized older people experience a steeper cognitive decline than community-dwelling people [7], as well as a drop in quality of life [8] and an increase in psychotropic drug use [9]. For these reasons, we need to study alternative and transitional care models between home care and nursing home care, such as foster families. Because fostered older people (while still moving out of their own homes) are taken care of within a family context instead of a nursing home or other collective settings, foster care placement processes could be an alternative to institutionalization. This model has developed to a greater extent over the last few years in Guadeloupe. Nearly 200 foster families care for about 300 dependent older people, whereas there are 21 nursing homes for approximately 1500 residents. Foster caregivers, after getting official approval and attending a 20-hour training course, usually accommodate 1 to 3 people in exchange for a monthly fee. Their mission is to ensure the well-being of their residents and to enable them to maintain close social and family relationships. Other professionals may also provide additional nursing care if necessary. Little is known about the characteristics of foster caregivers and their residents. Two decades ago, a study from Cébula and Horel [10] showed that 61% of fostered older people were older than 80 years in France, and two-thirds were women. Every 6 of 10 older people lived at home or with their own family before entering foster care, and foster care was requested by the older person’s household in 63% of cases. Most foster caregivers were women (96%). Two-thirds of the foster caregivers were between 40 and 60 years old, and 16% of them were older than 60 years. Every 8 of 10 foster caregivers were “partnered people,” the majority of them being single-family home owners (95%). Nearly half of the foster caregivers were in a nonemployment situation (inactive, unemployed, integration, and training) before obtaining their foster caregiver license. The cost of foster family accommodation for seniors depends on the number of caregiving hours, because of the length and frequency of stay (in 94% of cases, it is a full time) and geographical location. The monthly fee includes rent, services rendered, a maintenance allowance, and a daily allowance. Monthly cost ranges from €1400 to €2100 (US $1521.98 to US $2282.97) per month [11].

Foster families have also been tried out in others countries (eg, United States, Belgium, Italy, Russia, and Finland), but few scientific studies have assessed its effectiveness and efficiency. A Cochrane meta-analysis published in 2015 compiled 10 studies comparing home care or foster care with nursing home care for 16,377 older participants [12]. Because of the methodological limitations of the studies included, the meta-analysis failed to determine whether or not this type of accommodation was the most efficient in terms of mortality reduction, physical function, quality of life, or hospitalization rates. Indeed, the available studies relied on small samples and had high risks of bias (design bias, evaluation bias), and the baseline characteristics of the participants were very heterogeneous. Three 30-year-old studies focusing on foster care in the United States were included [13-15]. Two of them are of interest [13,15]. Braun and Rose [13] compared 269 older participants: 100 lived in foster care, 101 in nursing homes, and 68 at home. After 3 months, Activities of Daily Living (ADL) scores only improved in the foster care group, and costs were lower than those for the other 2 groups (US $28 per day vs US $74 for nursing homes and US $45 for home). There was no difference in morbidity, defined as the number of infections, injuries, skin problems, and hospitalizations. In their randomized study on 112 participants in foster care or nursing homes, followed for 12 months, Oktay and Volland [15] found no difference in mortality rates between settings (32.0% vs 28.8%). Stabilization or improvement of ADL and cognitive status, as well as overall lower health care expenses (25% less), was in favor of foster care. Nevertheless, nursing home residents’ level of satisfaction compared favorably with that of foster family residents. In any case, available data are scarce, assessed with short follow-ups, lack essential clinical outcomes, and definitely need to be updated.

To date, we do not know whether foster care is an alternative to nursing home care, as suggested by the limited existing literature, or a transitional care setting between home care and nursing home care. Epidemiological and medicoeconomic data on older people in foster families are essential to assess the relevance of this type of care, in particular, according to the severity of dementia or the degree of dependence in ADLs. Several issues need to be clarified: what is the residents’ annual hospitalization rate and the associated costs? What is the health care pathway of residents in terms of consultations with general practitioners, specialists, and paramedics? What is the prevalence of geriatric syndromes in this population, and the incidence of mortality? What is the incidence of pneumonia, the leading cause of death and emergency hospitalization in older people? What is the quality of life of the residents and their foster caregivers? The Karukera Study of Ageing in Foster Families (KASAF) is a prospective cohort study, designed to investigate these questions. This longitudinal study will assess the health status and medical and economic data of 250 foster family residents and their foster caregivers over a year.

## Methods

### Overview

The KASAF is a prospective, longitudinal cohort carried out in Guadeloupe (French West Indies), France, among foster families for older adults. This study will collect the socio-medico-economic data of older residents of foster families over a year, with a focus on hospital admissions. We will collect data using face-to-face interviews with the participants and their foster caregivers at baseline and after 6 and 12 months, and using phone interviews with the foster caregivers after 3 and 9 months.

### Objectives

This study is an epidemiological study that aims to explore the characteristics of foster family residents and caregivers. We have identified a number of outcomes that may provide insight on their profile. As hospitalization is the main expensive item in the health trajectories of older people [16], the primary objective of the KASAF is to study hospital admission rates of residents of foster families over a year.

Several secondary objectives are also targeted: length of hospital stays during the 12-month follow-up period; number of consultations with a general practitioner, a medical specialist, or a paramedical professional; global cost of hospital stays; prevalence of geriatric syndromes (frailty, undernutrition, depressive symptoms, incontinence and dependency, sensory impairments; falls; polypharmacy; bedsores; and cognitive impairment); incidence of lower respiratory tract infection; quality of life of foster care recipients and their foster caregivers; and burnout in foster caregivers.

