### Study Sample

A total of 250 residents will be recruited over 6 months among the 300 older residents currently in foster families. The primary end point will be the hospitalization rate at 12 months. A 30% hospital admission rate over a year has been reported in the Incidence of pNeumonia and related ConseqUences in nursing home Resident study in nursing home residents [16]. A change in the hospitalization rate from 30% to 15% would be considered as significant from a clinical and public health point of view. For an risk of 5% and 250 participants, the expected CI will be 4.4% for a hospitalization rate of 15% and 5.7% for a 30% rate.

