#### Data Collection

At inclusion, nurses, geriatricians, and psychologists will collect sociodemographic, health-related, and psychosocial information. The inclusion visit is the first on-site interview and will be followed by 4 visits: 2 on-site visits 6 and 12 months after the inclusion visit, and 2 phone interviews 3 and 9 months after the inclusion visit (Table 1).

The interviewers will be conducted by health care professionals: psychologists, interns, and nurses, trained by the INSERM Team SEPIA (UMR 1219) from the University of Bordeaux, a team having expertise in implementing cohort studies.

**Table 1 table1:** Expected timeline for the KASAF^a^.

Time line	Goal
July-September 2020	Ethics Committee approval Registration on ClinicalTrials.gov
September 2020	Training sessions for the interviewers
November 2020-May 2021	Inclusion period
February 2021-February 2022	3-, 6-, and 9-month follow-up
February 2022-May 2022	End of 12-month follow-up (end of data collection)
June 2022-March 2023	Data analysis
From May 2023	Scientific communications

^a^KASAF: Karukera Study of Ageing in Foster Families.

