#### Primary Outcome

The main outcome is the number of hospitalizations over a year. The French hospital discharge database (PMSI) will provide information on hospital admissions. This information will be retrieved with the approval of the participants or their legal representative. Information on hospital admissions will also be collected from the foster caregiver for confirmation.

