#### Expected Timeline

The first participant was included on November 16, 2020. The 1-year follow-up was ended in June 2022 (Table 1).

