### Data Analysis

First, the analysis will describe the number of included participants, the inclusion curve (evolution of the number of people included between the first and last inclusion), the number of theoretical visits, the number of visits actually made, and the ratio of both (number of visits made or number of theoretical visits).

A description of the rate and causes of death and study dropout will also be provided.

The following quantitative variables described in terms of number of staff, mean, and interindividual SD and 95% CI of the mean, median, range, and IQR values: number of hospitalizations, total length of hospitalization, total cost related to hospitalizations, total number of consultations with a general practitioner, total cost of low respiratory infections, total number of falls, MMSE score, total number of drugs, NPI score, QoL-AD score, SF-36 score, and Pro-QoL score.

Qualitative variables (ordinal: AGGIR grid, feeling of loneliness; dichotomous: vital status; presence or absence: frailty syndrome, depression, undernutrition, visual impairment, hearing impairment, incontinence, ADL dependency, IADL dependence) of participants at inclusion will be described in terms of frequency and number.

Comparisons between the 3 times (T0, T6, and T12) will be performed using repeated-measures ANOVA for quantitative variables and the Cochran-Armitage test for trend for qualitative variables.

Statistical analyses will be performed using the RStudio software (version 2.7; Posit Software).

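### Admissions, hospital days and cost are summarised as a mean per resident with no time at risk, so with deaths the summary falls below the yearly rate that the objective names

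*Protocol article*

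**What the plan says.** The Objectives section of the Protocol article states a rate: "the primary objective of the KASAF is to study hospital admission rates of residents of foster families over a year". Two later sections make this concrete in different ways. Study Sample has "The primary end point will be the hospitalization rate at 12 months" and sizes it as a proportion, with 15% and 30% as the reference values. Primary Outcome has "The main outcome is the number of hospitalizations over a year", which is a count.

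The Data Analysis section lists how quantitative variables will be described: "mean, and interindividual SD and 95% CI of the mean, median, range, and IQR values: number of hospitalizations, total length of hospitalization". Total hospitalization cost is in the same list. The section also promises a description of deaths and dropouts, but as a separate item that is not linked to the admission outcome. It gives no person-time denominator. It also does not say how a resident observed for less than 12 months enters these summaries.

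The data needed for time at risk are planned. Admissions come from the hospital discharge database (PMSI), vital status is checked at months 3, 6, 9 and 12, and the date of death is sought where possible (Primary Outcome, Secondary Outcomes, Phone Interviews).

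**The concern.** A mean count per resident can be read as a yearly rate only when every resident contributes a year. These are dependent older people, and the only 12-month mortality figures in the article are high. They come from a randomized study of foster care against nursing homes, which "found no difference in mortality rates between settings (32.0% vs 28.8"%). A resident who dies at month 4 can be admitted during four months only, yet has the same weight in the mean as one observed for twelve.

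This matters most for comparison. The Abstract and the Discussion intend to set hospitalization, mortality and cost beside those of a twin nursing-home study, and the Discussion expects the data to inform resource allocation. If two settings admit residents equally often while they are alive, the one with more deaths will show fewer admissions, fewer days and lower cost per resident. That difference would reflect shorter survival and could be mistaken for less use of hospital care.

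**Working it through.** **The plan's own figure.** Inputs from Study Sample: 250 residents, 5% risk, rates of 15% and 30%. The half-width of a 95% Wald interval is 1.96 × √(p(1−p)/n).
- p = 0.15: 1.96 × √(0.15 × 0.85/250) = 0.0443, stated as 4.4%.
- p = 0.30: 1.96 × √(0.30 × 0.70/250) = 0.0568, stated as 5.7%.

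Both reproduce. They are simple proportions with all 250 residents in the denominator and no term for death or dropout.

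**Mean per resident against rate per person-year alive.** With total events E, N residents and total person-years PY, the mean is E/N and the rate is E/PY. Their ratio is PY/N, the mean exposure. This identity does not depend on how admission and death are related. Only the value of PY/N needs an assumption. With a constant death hazard h = −ln(1−m) and 12-month mortality m, and no other loss, PY/N = m/h.

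| m | Source | h | PY/N | Mean below rate by |
|---|---|---|---|---|
| 10% | assumed | 0.105 | 0.949 | 5.1% |
| 20% | assumed | 0.223 | 0.896 | 10.4% |
| 28.8% | Introduction | 0.340 | 0.848 | 15.2% |
| 32.0% | Introduction | 0.386 | 0.830 | 17.0% |

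**What this does to a comparison.** Suppose two settings each have 0.4 admissions per person-year alive (assumed), with mortality of 10% in one and 28.8% in the other. The means per resident are 0.4 × 0.949 = 0.380 and 0.4 × 0.848 = 0.339. The second is lower by 1 − 0.848/0.949 = 11%, although admission intensity is identical.

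**The proportion admitted at least once.** Let l = −ln(1−p), where p is the 12-month admission risk without deaths, and let death be independent of admission. The cumulative incidence with death competing is l/(l+h) × (1 − e^−(l+h)).
- p = 30%: 28.6%, 27.1%, 25.7% and 25.2% at the four mortalities above.
- p = 15%: 14.3%, 13.5%, 12.8% and 12.5%.

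These are the proportions that would actually be seen. They are a valid description of what happens to residents in a year, but they too move with mortality and should be read beside it.

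**Do those who die look like low users?** Mean survival of those who die within the year is 1/h − (1−m)/m, which is 0.491 year at m = 10% and 0.468 year at m = 32%. Their mean count is below that of survivors only if their admission intensity while alive is less than 1/0.491 = 2.0 to 1/0.468 = 2.1 times that of survivors. At m = 28.8% and 0.4 per year in survivors, the mean count in those who die is 0.19, 0.38 and 0.57 at intensity ratios of 1, 2 and 3, against 0.40 in survivors.

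**The case against.** The article is condensed, its statistical analysis plan is not shown, and time at risk is often handled there. Data Analysis lists descriptive statistics and does not name the mean as the estimator of the hospitalization rate. Mean days or cost per enrolled resident over a year is also a legitimate quantity in its own right. The mortality of about 30% comes from one study of 112 participants, among three that the article itself calls 30 years old, and is not a planning assumption here. The nursing-home comparison is conditional on similar residents and lists mortality as well.

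Much of this stands, and it limits the claim. What remains is that the only summary stated for the primary count is per resident, while the stated objective is a yearly rate. That is a stated choice, not merely an omitted detail.

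Three stronger readings are tempting, and the article does not support them.
- That the hospitalization rate is biased downward. On the proportion scale of Study Sample, with all residents in the denominator and complete follow-up, the result is a valid cumulative incidence with death as a competing event. The shortfall holds only against a rate per person-year alive.
- That residents who die early always look like low users. This reverses if they are admitted at more than about twice the intensity of survivors.
- That early participants are observed for about 15 months, inferred from "The first participant was included on November 16, 2020" and the Table 1 row "End of 12-month follow-up (end of data collection"), which starts in February 2022. Table 1 gives calendar phases for the cohort. Data Collection sets the last visit 12 months after each resident's inclusion, and the outcome sections refer to one year. Nothing says that later events are counted.

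Nor does the article say that only those who complete the 12-month visit will be analysed.

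**Conclusion.** The point holds in a limited form. For number of hospitalizations, total stay and total cost, the stated mean per resident does not deliver the yearly rate in the objective once residents die. It is lower than the rate per person-year alive by about 5% at 10% mortality, 10% at 20%, and 15% to 17% at 28.8% to 32.0%. The direction follows from arithmetic alone. The size rests on a constant death hazard and on mortality figures that are either assumed or taken from one old study. The main consequence is that settings with different mortality cannot be compared on this mean. The proportion scale of Study Sample is sound, provided that residents who die stay in the denominator and follow-up is complete. The article does not state either condition. Dropout may matter less than death, because discharge records may still be retrievable after a missed visit, but the article does not settle this.

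**What to change.** In Data Analysis:
- Count admissions, days and cost from inclusion to the earliest of 12 months, death or loss to follow-up. State whether PMSI records are still used after a missed visit, since this decides when a resident counts as lost.
- Report admissions, days and cost per person-year alive. For admissions, use a count model with log person-time as offset.
- Define the Study Sample end point as the 12-month cumulative incidence of first admission with death as a competing event (Aalen-Johansen), keeping residents who die in the denominator.
- Show 12-month mortality beside both results, and use the same definitions in the nursing-home study.

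The per-resident means may stay as additional description, labelled as such. No new data collection is needed: admissions come from PMSI and dates of death are already sought. Where a date is missing, the three-monthly vital status checks bracket it. The cost is slightly more analysis and a few sentences of text.
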